## Abstract

**Background:**

Chronic low back pain is considered to be one of the main causes of absenteeism from work and primary and specialized consultations. The symptoms of nonspecific chronic low back pain may be accompanied by the activation of myofascial trigger points in the muscles, together with local and/or referred pain. Electrical dry needling is increasingly used in the treatment of lumbar myofascial pain. Conventional physiotherapy, however, is a popular approach to chronic pathologies, and there is evidence of different modalities of physiotherapy being used in the treatment of chronic low back pain. The aim of this study has been to determine the effectiveness of electrical dry needling versus conventional physiotherapy when applied to active and latent myofascial trigger points in patients with nonspecific chronic low back pain.

**Methods:**

This is a controlled, randomized, two-arm, double-blind study. A total of 92 patients with chronic low back pain (time to onset ≥ 3 months, Roland Morris Disability Questionnaire score ≥ 4) will be recruited from the University of Almería. Participants will be divided into two study groups (*n* = 40) to receive treatment of low back pain with electrical dry needling and conventional physiotherapy (ischaemic compression, analytic stretching and postural education training dossier). A total of 6 sessions will be administered once a week for 6 weeks. Pain intensity, disability, fear of movement, quality of life, quality of sleep, anxiety and depression, pressure pain threshold, abdominal strength and lumbar mobility will be recorded at 6 weeks (post-immediate) and 2 months after the end of treatment.

**Discussion:**

We believe that an approach including electrical dry needling to chronic low back pain dysfunction will be more effective in these patients. The results of this study will inform clinicians on which type of treatment is more beneficial for patients with chronic low back pain.

**Trial registration:**

ClinicalTrials.gov NCT04804228. Registered on 14 January 2021

**Supplementary Information:**

The online version contains supplementary material available at 10.1186/s13063-022-06179-y.

## Background

Low back pain is a major public health problem in industrialized countries that causes individual suffering, absenteeism from work and, in some cases, early retirement. Since it is a common pathology that is difficult to treat effectively, low back pain represents a high economic burden for both society and the health system [1–3] and is considered one of the main causes of primary and specialized care consultations [4]. In Europe, the direct and indirect costs of low back pain account for between 1.7 and 2.1% of the annual gross domestic product [8, 9].

Back pain, which affects up to 23% of the population worldwide, is the most common chronic disease in people under 65 years of age. With a lifetime prevalence of up to 85% in industrialized countries [3], estimates suggest that between 24 and 80% of patients have at least one recurrence per year, being more frequent and persistent in older adults [2, 5, 6]. In any given 6-month period, 72% of adults in the general population will report low back pain, and 11% will report disabling low back pain [7].

Pain intensity, degree of pain interference with activities of daily living (resulting in disability), and health-related quality of life are among the primary outcomes in studies in patients with low back pain [1]. In the 2010 Global Burden of Disease Study, which includes 291 diseases, low back pain ranked first in terms of disability and sixth in terms of overall burden [10]. In addition to age, psychological factors such as emotional distress and dysfunctional pain coping mechanisms play an important role in the development and/or persistence of nonspecific chronic low back pain (CLBP) [6].

The symptoms of CLBP may be accompanied by the activation of myofascial trigger points (MTrPs) in the lumbar and proximal muscles, together with local and/or referred pain [11, 12]. Clinically, MTrPs present as palpably taut bands with a local twitch response and pain on pressure [12–14]. When the points are active, digital palpation causes pain to radiate to a distant site (referred pain); when they are latent, palpation may be locally painful, but no radiation occurs (local pain) [11, 12].

The MTrPs of each muscle have their own characteristic pain pattern; therefore, the spread of the pain can help identify the muscles that may contain active and latent trigger points [15]. CLBP is associated with the presence of MTrP in the quadratus lumborum muscle, and often also in the lumbar and superficial paraspinal multifidus muscles [13].

Noninvasive treatment options for CLBP remain controversial, and there is no general consensus on the best approach [16]. Some trials in CLBP and electrical dry needling conclude that there is still no strong evidence to support the clinical effectiveness of electrical dry needling on LBP versus any other treatment modality [17–20].

Dry needling is typically used to treat soft tissues, such as muscles, ligaments, tendons, fascia, scar tissue, peripheral nerves and neurovascular bundles involved in a variety of neuromusculoskeletal pain syndromes [21, 22]. Dry needling involves the insertion of fine monofilament needles without the use of injectables, and its therapeutic effect is based on stimulating specific reactions in the target tissue [23–27]. It is a relatively new treatment modality used by physical therapists around the world as part of the complex treatment of chronic musculoskeletal pain [23]. The effectiveness of this approach has been confirmed in numerous studies and systematic reviews on the management of chronic lumbar MTrPs and myofascial pain [28–30]. In electrical dry needling, needle electrodes are used to deliver an electric current to the taut muscle band or the pain-generating MTrP [25, 26, 31] Low-frequency currents are thought to improve the physiological effects of the therapy by using electrical stimulation to enhance certain physiological reactions and achieve a speedier analgesic and anaesthetic effect than that obtained with standard dry needling in patients with low back pain [32, 33]. Despite the popularity of electrical dry needling in clinical physiotherapy, there is insufficient scientific evidence to show its therapeutic effects in the treatment of CLBP [16, 34, 35].

Various treatment approaches beyond the scope of physiotherapy have been proposed to reduce the recurrence of low back pain and its associated care costs. Clinical practice guidelines provide strong evidence that cognitive behavioural therapy, exercise, spinal manipulation and rehabilitation with various physiotherapy procedures are all moderately effective in chronic or subacute low back pain (> 4 weeks duration) [34–36]. Recent systematic reviews and meta-analyses recommend exercise therapy to improve back strength, flexibility, range of motion and fitness in chronic low back pain [37–39]. However, there is no evidence to show whether invasive approach like the electrical dry needling is more effective than a conventional physiotherapy in patients with nonspecific CLBP.

## Study objectives

The objective of this randomized controlled trial is to evaluate the effectiveness of electrical dry needling versus conventional physiotherapy in the treatment of patients with nonspecific chronic lower back pain.

The specific objectives are (i) to compare the effectiveness of electrical dry needling versus conventional physiotherapy in improving pain, functionality, lumbar spine mobility and quality of life in patients with nonspecific chronic low back pain and (ii) to evaluate the effect of this therapy on active myofascial trigger points in terms of the pressure tolerance threshold following electrical dry needling versus conventional physiotherapy.

## Methodology

### Study design and ethical approval

This is a controlled, randomized, two-arm, double-blind study comparing (i) patients with chronic low back pain treated with electrical dry needling and (ii) patients with chronic low back pain treated with conventional physiotherapy consisting of ischaemic compression, analytical stretching and a dossier of home lumbar spine exercises. Study participants will be randomly assigned to two groups (electrical dry needling group or conventional physiotherapy group) with a 1: 1 ratio.

This protocol has been drawn up following the Standard Protocol Items: Recommendations for Interventional Trials (SPIRIT) (Additional file 4). The study will be carried out in partnership with the physiotherapy department of the University of Almería. Ethical approval for this trial was granted by the University of Almería Research Ethics Committee (UALBIO2020/044). The study protocol was registered in an international clinical trial registry, ClinicalTrials.gov (protocol number NCT04804228).

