### Participants

A total of 92 patients aged between 30 and 65 years, diagnosed with nonspecific chronic low back pain lasting more than 3 months [40] who are not currently undergoing any type of treatment, will be recruited. Patients will be randomized to two treatment groups (electrical dry needling or conventional physiotherapy). Participants will receive treatment once a week for 6 weeks in the physiotherapy laboratories of the University of Almería, with a follow-up evaluation at 6 weeks and 2 months after the start of treatment. During their first visit, participants will be screened for study eligibility according to the study inclusion and exclusion criteria and will be assessed by a therapist blinded to the interventions. After this face-to-face evaluation, patients will be randomly assigned to one of the two groups and will receive the corresponding treatment for low back pain administered by two researchers trained in the techniques used. All participants will sign the informed consent form, which complies with the Declaration of Helsinki of the World Health Organization (schedule of enrolment, interventions and assessments is shown in Fig. 1).

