### Randomization and blinding

Participants will be randomized to two groups using a computer-generated (Epidat 4.2) table of random numbers generated. After randomization, participants will be assigned to either the experimental electrical dry needling group or the conventional physiotherapy control group in a ratio of 1:1. Randomization will be performed by the principal investigator.

There will be 46 participants in each group. The randomly generated group allocations will be placed in sealed opaque envelopes before being delivered to the participants and stored in locked cabinets.

The outcome assessor and study statistician will be blinded to the entire process. The outcome assessor will make no attempt to guess the participant’s treatment group. The computer-generated outcome measures transmitted to the statistician will not contain any information that identifies the patient’s group.

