#### Primary outcome measures

The following are the primary outcome measures:
Roland Morris Disability Questionnaire (RMDQ): This self-reported questionnaire consists of 24 items that rate limitations in different activities of daily life attributed to low back pain, such as walking, bending over, sitting, lying down, dressing, sleeping, personal care and daily activities. Disability is rated from 0 points (best) to 24 points (worst) [46].Oswestry Disability Index (ODI): The Oswestry Disability Index assesses the limitations in activities of daily living in 10 dimensions, each rated on a 6-point scale (0–5 points). The higher the score, the greater the disability. The overall score is expressed as a percentage and is used to classify people as minimally disabled (0–10%), moderately disabled (20–40%), severely disabled (40–60%), crippling back pain (60–80%) or bedridden (80–100%) [47].Visual analogue scale (VAS): Study participants will indicate the intensity of their pain on a 100-mm VAS. They are asked to situate their pain on a 100-mm horizontal line, where 0 mm indicates “no pain”, and 100 mm indicates “the worst pain imaginable” [48].

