### Ethics and dissemination

All participants will receive verbal and written information about the study before giving their consent to participate. They will be informed that they can leave the study at any time. Participants who agree to take part in the study will sign two copies of the informed consent form, one for the research and evaluation team and one for the participant.

All hard copies will be confidential and stored in a locked filing cabinet in the research group office and in electronic format in a password-protected database. The research team will monitor the integrity of the trial data. All participants, group assignments, treatment records and sociodemographic data will be coded, and the results of the questionnaires will be scored.

The data collected on each participant will be kept under lock and key by the evaluator. If the data are in digital format, they will be stored in a computer with a secret access code known only to the evaluator.

The eligibility criteria, results and analyses will not be modified once the first participant has been enrolled in the study. Any amendment to the protocol, including changes in the eligibility criteria, the results or the analyses, will be communicated to the Institutional Research Committee of the University of Almería and reported in articles and presentations disseminating the results of the trial.

The feasibility results will be published in peer-reviewed journals and presented at academic, clinical and health services conferences.

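### The trial is labelled double-blind, but only the outcome assessor and the statistician are blinded, and all three primary outcomes come from patients who can tell which treatment they receive

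*Protocol article*

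**What the plan says.** The design section (Study design and ethical approval) opens with "This is a controlled, randomized, two-arm, double-blind study", and the Methods part of the abstract uses the same label. Neither place says who is blinded.

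Randomization and blinding does say: "The outcome assessor and study statistician will be blinded to the entire process". It adds that the data passed to the statistician carry nothing that identifies the group. The Participants section states that at the first visit patients "will be assessed by a therapist blinded to the interventions", and that treatment is "administered by two researchers trained in the techniques used". No section states that patients or treating therapists are blinded, and no sham or other masking is described.

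The primary outcomes are the RMDQ, the ODI and a 100-mm pain VAS. Of the RMDQ the article says "This self-reported questionnaire consists of 24 items". The VAS is marked by the participant. The ODI is described as a score of limitations in daily living over 10 dimensions, without any rating by an assessor.

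**The concern.** A reader who meets the label double-blind will normally take it that patients do not know their treatment, and will discount expectation as an explanation for a difference. Here that assurance is missing exactly where it would matter most. The primary outcomes are pain and disability as the patient reports them, and the comparison sets an invasive electrical technique against manual treatment and exercises. The Discussion part of the abstract also records the investigators' belief that needling will prove more effective. If patients come to share that belief, it can move RMDQ, ODI and VAS scores whatever the treatments do to the back.

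At stake is how a result is read and graded. A difference would be taken as protected by blinding when it is not.

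**Working it through.** No figure in the protocol is in dispute. The check compares the label with the procedures.

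**Step 1: who is blinded**

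| Party | Stated status | Source |
|---|---|---|
| Outcome assessor | blinded | Randomization and blinding |
| Statistician | blinded | Randomization and blinding |
| Therapist assessing at first visit | blinded | Participants |
| Patients | no statement | – |
| Two treating researchers | no statement | – |

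**Step 2: could patients and treating therapists be blind in practice?**

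- Electrical dry needling group: needles are inserted into trigger points, connected to a 2 Hz current and left for 30 min. The intensity is set by what the patient says they feel.
- Conventional physiotherapy group: thumb pressure on each trigger point, analytical stretching, and home exercises 5 days a week recorded in a booklet.

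A patient cannot confuse these two, and neither can the person delivering them. The article never says outright that patients and therapists are unblinded. That is an inference from the interventions, but nothing in the text points the other way.

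**Step 3: does the blinding that exists reach the primary outcomes?**

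| Primary outcome | Who supplies the score | Protected by assessor blinding? |
|---|---|---|
| RMDQ | patient (stated to be self-reported) | no |
| VAS | patient (marks the line) | no |
| ODI | patient (inferred; no assessor rating described) | no |

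The count is 3 of 3. Blinding the statistician guards against selective analysis; it does not alter what a patient has already reported.

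**Step 4: illustration of what a reporting bias could do**

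The documents give no size for such a bias, so the values of b below are assumptions. Suppose there is no true effect and the mean RMDQ difference is shifted by b points through expectation alone. Completers per arm: 46 × 0.85 = 39.1, taken as 39 (46 per group and 15% loss are the protocol's figures). The Sample size section gives both an SD of 2.5 and a variance of 10, so both SDs are shown: 2.5 and √10 = 3.16.

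- SE = SD × √(2/39). For SD 2.5: 2.5 × 0.2265 = 0.566. For SD 3.16: 0.716.
- Two-sided rejection rate at 5% = 1 − Φ(1.96 − b/SE) + Φ(−1.96 − b/SE), with Φ the standard normal distribution function.
- Example, b = 1.0 and SD 2.5: b/SE = 1.766, and 1 − Φ(0.194) ≈ 0.42; the other tail is negligible.

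| Assumed bias b (RMDQ points) | SD 2.5 | SD 3.16 |
|---|---|---|
| 0 | 5% | 5% |
| 0.5 | 14% | 11% |
| 1.0 | 42% | 29% |
| 1.5 | 75% | 55% |

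Each assumed bias is smaller than the 2.5-point difference that the trial is sized to detect. The table shows sensitivity only. It is no estimate of the bias in this trial, and the conclusion does not depend on it.

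**The case against.** The strongest reply is that the article explains its own label. It has a section on blinding that names exactly two blinded parties, and it nowhere claims that patients are masked. Masking could not be achieved between these two treatments in any case. That is fair as far as it goes: a careful reader of the methods can see who is blinded, and the lack of patient blinding is no lapse of conduct. It does not save the label. The abstract and the design section carry it without explanation, and on the assessor-plus-statistician reading the blinding still does not reach the primary outcomes.

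Four stronger readings may occur to a reader, and the documents do not support them.

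- *The missing sham is a design error.* Study objectives asks how needling compares with conventional physiotherapy. That is a comparative-effectiveness question between two active treatments, and it needs no sham. The limit falls on interpretation only.
- *The assessor's own blinding is compromised by data custody.* Ethics and dissemination says "The data collected on each participant will be kept under lock and key by the evaluator". The same section says that group assignments and treatment records are coded. It does not give the evaluator the allocation list or the exercise booklets, and randomization rests with the principal investigator. The wording on custody could be clearer, but a breach cannot be read from it.
- *The physical secondary outcomes are safe because the blinded assessor measures them.* Trunk flexion stops at pain or limitation, the McQuade test times how long the patient holds a position, and algometry records a pain threshold. All three depend partly on the patient's response or effort, so the secondary outcomes do not divide cleanly into protected and unprotected.
- *The envelopes prove that patients are told their arm.* That the allocations "will be placed in sealed opaque envelopes before being delivered to the participants" describes concealment of allocation. Patients' awareness follows from the treatments themselves.

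**Conclusion.** The point holds and the label is wrong as written. The article claims a double-blind design, while its procedures blind the outcome assessor and the statistician only. All three primary outcomes are reported by patients who can tell their treatment, so assessor blinding does not protect them from expectation bias.

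This rests on two inferences, both well supported: that needles with current cannot be mistaken for compression, stretching and exercises, and that the ODI is completed by the patient although the text does not use that word. The amount of bias cannot be estimated from the documents.

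The conclusion concerns the stated design property and how the primary result is to be read. It does not find fault with the comparator, the randomization or the blinding of the assessor.

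**What to change.** 1. In the Methods part of the abstract and in Study design and ethical approval, replace double-blind with: outcome assessor- and statistician-blinded; participants and treating therapists not blinded.
2. State beside the primary outcomes that RMDQ, ODI and VAS are unblinded self-reports, so that a between-group difference is to be interpreted as the effect of the whole treatment package, including expectation.
3. Use the same description in any report of results.

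The cost is wording and a less favourable design label. Eligibility, outcomes, data collection and analysis stay as they are, so the change does not touch the elements that Ethics and dissemination fixes at first enrolment.

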### Participants

A total of 92 patients aged between 30 and 65 years, diagnosed with nonspecific chronic low back pain lasting more than 3 months [40] who are not currently undergoing any type of treatment, will be recruited. Patients will be randomized to two treatment groups (electrical dry needling or conventional physiotherapy). Participants will receive treatment once a week for 6 weeks in the physiotherapy laboratories of the University of Almería, with a follow-up evaluation at 6 weeks and 2 months after the start of treatment. During their first visit, participants will be screened for study eligibility according to the study inclusion and exclusion criteria and will be assessed by a therapist blinded to the interventions. After this face-to-face evaluation, patients will be randomly assigned to one of the two groups and will receive the corresponding treatment for low back pain administered by two researchers trained in the techniques used. All participants will sign the informed consent form, which complies with the Declaration of Helsinki of the World Health Organization (schedule of enrolment, interventions and assessments is shown in Fig. 1).

**Fig. 1 Fig1:**
[figure not shown]
Design and flow of participants through the trial. RMQ, Roland-Morris Low Back and Disability Questionnaire; ODI, Oswestry Disability Index; VAS, Visual Analogue Scale; TSK, Tampa Scale for Kinesiophobia

#### Inclusion criteria

Both male and female patients aged between 30 and 65 years with chronic low back pain lasting 3 months or more, with a low back pain disability score ≥ 4 on the Roland-Morris Disability Questionnaire (RMQ) and not receiving any other physiotherapy treatment are eligible for inclusion.

